Each untreated patient derived in step 3 (n~6000) will be matched 1:1 with the FP/SAL-treated patient record from step 4 with the closest propensity score (~12 000) giving us an analysis population for objective 1 of ~12 000 patients—double the size of TORCH (figure 2). For those individuals that have contributed multiple exposed records to the pool of CPRD-exposed participants (figure 3), after one of their exposed records has been propensity-score matched to an unexposed participant, we will remove all other exposed records for that individual from the remaining pool of CPRD-exposed participants. This will mean that an individual can only appear once as an exposed participant in the final propensity-score matched cohort.

We will also apply an alternative additional approach for objective 1, where instead of generating and using propensity scores to obtain a final analysis population at steps 5 and 6, we will match records from our exposed TORCH-eligible cohort with participants from the TORCH trial to create a TORCH-analogous exposed patient cohort. This will then be combined with the TORCH-analogous unexposed patient cohort to create a final analysis population (with multivariable regression techniques used to account for confounding instead of propensity scores).

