### Sample size

#### Objective 1

Assuming a baseline conservative exacerbation rate of 0.5 per patient per year,^10^ we would only require a sample of 408 patients per treatment group to detect a reduction in annual exacerbation rate to 0.4 per year, with 80% power and 5% significance. The estimated sample size is ~12 000, which will provide ample power for the main outcomes of interest, and allow stratification by patient characteristics to determine stratified results, and will also be ample for the secondary analyses where we will use 99% CIs. For example, to detect a reduction from 0.5 to 0.4 exacerbations per year with 80% power and 1% significance we would need ~600 people in each treatment group.

#### Objectives 2 and 3

We are also confident that we will have sufficient numbers to allow well-powered analyses for objectives 2 and 3. For example, a feasibility count looking at the number of people over the age of 80 eligible for inclusion in objective 2 estimated that there would be >2000 people in each exposure group.

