#### Methods of analysis

For all objectives, comparisons will be made according to FP/SAL (or other drugs being analysed as specified in the ’Exposures' section) status for rate of COPD exacerbation, pneumonia and mortality over 3 years. All analyses will be performed according to the ‘intention-to-treat’ principle (as was done in the TORCH study), meaning that if a participant enters the study as either an exposed or unexposed participant, they will remain assigned to that exposure category for the entire duration of their follow-up (irrespective as to whether their true exposure status changes). For exacerbations, a negative binomial model will be used, accounting for variability between patients in the number and frequency of exacerbations, with the number of exacerbations as the outcome and the log of treated time as an offset variable. Time to mortality, first pneumonia and treatment change will be analysed using Cox proportional hazards regression. This mirrors TORCH end points of major benefit and harm. We anticipate the propensity matching process will allow us to assemble treated and untreated groups that are very similar with respect to baseline characteristics except FP/SAL treatment status. However, this will be tested by assessing standardised differences for each baseline variable. If substantial differences are noted for important variables, it may be necessary to further adjust the statistical models. This could also include examining the effect of using greedy versus optimum matching approaches in order to obtain the closest propensity score match and/or matching at a ratio other than 1:1.^17^

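### In the propensity-matched analyses, covariate adjustment is left to discretion after a balance check, so smaller measured imbalances stay in the rate ratio used for validation

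*Protocol article*

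**What the plan says.** Under Selection of participants, Objective 1, step 6, each of about 6000 untreated patients, already matched to a TORCH participant, is "matched 1:1 with the FP/SAL-treated patient record from step 4 with the closest propensity score". The treated pool holds about 12 000 patients and, by step 4, has not been matched to TORCH.

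Under Methods of analysis, "For exacerbations, a negative binomial model will be used", and the time-to-event outcomes use Cox regression. The authors expect the matched groups to be similar, and "this will be tested by assessing standardised differences for each baseline variable". What follows a poor result is conditional: "If substantial differences are noted for important variables, it may be necessary to further adjust the statistical models". Other responses mentioned there are a different matching algorithm or a ratio other than 1:1.

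Under Validation of results against TORCH, the exacerbation rate ratio must lie between 0.65 and 0.9 with a 95% CI that excludes 1. If FP/SAL is compared with SAL, the band is 0.81 to 0.95. The section expects the effect in routine care to be possibly weaker than TORCH's 0.75.

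Two further passages matter. Step 6 and the propensity score section describe an additional objective 1 analysis in which both groups are matched to TORCH and confounding is handled by multivariable regression. The Covariates section says that the candidate propensity score variables all come from CPRD. That list does not name exacerbation history, which step 3 uses for matching to TORCH.

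**The concern.** In the propensity-matched analysis the default outcome model has no covariates. Imbalances that are each judged acceptable remain in the estimate. If several point the same way on the prognostic scale, they add up. With about 6000 per group the standard error is small, so a modest bias can be large relative to the confidence interval.

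The objective 1 rate ratio feeds a pass/fail decision. A result outside the band also sets off further work: the SAL comparator, the grace-period analysis and, above 0.9, the adherence restriction. Objectives 2 and 3 reuse propensity matching and the same analysis section, so the default applies there too. The covariates that would remove the measured part of the bias are already to be extracted.

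**Working it through.** **1. The plan's own figure.** The 408 per group (0.5 versus 0.4, 80% power, 5%) reproduces as a two-sided comparison of two proportions with continuity correction. Without correction, n = [1.96·√(2·0.45·0.55) + 0.842·√(0.5·0.5 + 0.4·0.6)]² / 0.1² = 388. With correction, (388/4)·[1 + √(1 + 4/(388·0.1))]² = 408. The same method at 1% gives 597, in line with the stated 600 or so. For this point the figure shows only that about 6000 per group is far above the stated requirement.

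**2. Precision at the planned size.** Inputs from the protocol: 6000 per group, 0.5 events per year, 3 years, rate ratio 0.75. Assumption: negative binomial dispersion k from 0.5 to 2.

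SE(log RR) = √{[1/(0.5·3) + k + 1/(0.5·0.75·3) + k]/6000}

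At k = 1 this is √(3.556/6000) = 0.0243, giving a 95% CI at 0.75 of 0.715 to 0.787. Over k = 0.5 to 2 the SE is 0.021 to 0.030.

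**3. Distance to the limits (log scale).**
- ln(0.75/0.65) = 0.143 and ln(0.9/0.75) = 0.182
- ln(0.9/0.85) = 0.057
- SAL band: ln(0.88/0.81) = 0.083 and ln(0.95/0.88) = 0.077

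**4. Bias from residual imbalance, rough rule.** Log bias ≈ number of covariates × standardised difference × ln(rate ratio per SD), all in one direction. Assumed ranges: difference 0.02 to 0.10, rate ratio per SD 1.2 to 2.0.
- One covariate: 0.02·ln 1.2 = 0.004 up to 0.10·ln 2 = 0.069, a factor of 1.004 to 1.07. A true 0.75 stays inside the band. At the top of the range a true 0.85 becomes 0.91.
- Two covariates at 0.10 with rate ratio 1.5: 2·0.10·ln 1.5 = 0.081. Then 0.75 becomes 0.69 or 0.81, 0.85 becomes 0.78 or 0.92, and 0.88 in the SAL comparison becomes 0.81 or 0.954.

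**5. Simulation of the matching itself.** 6000 untreated and 12 000 treated, logistic propensity score, greedy nearest match without replacement or caliper, negative binomial counts (1.5 expected untreated events over 3 years before covariate effects, dispersion 0.7). Assumptions: five prognostic covariates with rate ratios 1.1 to 1.3 per SD; treated patients differ before matching by the amount shown on each. True RR 0.75. Ranges in the first two rows are across runs of 120 and 60 replicates; the last three rows used 40.

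| Difference before matching | Largest residual difference | Unadjusted RR | Coverage | Adjusted RR | Coverage |
|---|---|---|---|---|---|
| 0.35 SD, same direction | 0.08 | 0.78 | 55–60% | 0.75 | 95–97% |
| 0.30 SD, same direction | 0.05 | 0.77 | 77–87% | 0.75 | 97% |
| 0.20 SD, same direction | – | 0.75 | – | – | – |
| 0.35 SD, three up and two down | 0.08 | 0.759 | 93% | – | – |
| 0.35 SD, pool of 15 000 | – | 0.766 | 88% | – | – |
| 0.35 SD, pool of 18 000 | – | 0.758 | 93% | – | – |

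Monte Carlo error on coverage is √(0.60·0.40/120) = 4.5 points and √(0.55·0.45/60) = 6.4 points, so only the pattern should be read. The simulated shift is somewhat below the rule in step 4, because the matched treated records also have a narrower covariate spread.

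**6. Does the pass/fail result change?** At a true 0.75, no: 0.78 passes. At a true 0.85 with the 0.35 SD setting, the unadjusted RR averages about 0.88 and exceeds 0.9 in about 20% of replicates. At a true 0.87 it averages 0.909 and exceeds 0.9 in 73% of 60 replicates, against 5% when adjusted. As a check with SE 0.0239 unadjusted, ln(0.909/0.9)/0.0239 = 0.42, a probability of about 66%. With SE 0.0225 adjusted, ln(0.9/0.87)/0.0225 = 1.5, about 7%.

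**7. Precision.** Adjustment cuts the SE by about 6% (0.0239 to 0.0225). Even at RR 0.9 the unadjusted upper limit is only 0.936 to 0.955 over 3 years (k = 0.5 to 2), so the requirement that the CI exclude 1 is not at risk.

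**The case against.** An unadjusted model after balance-checked propensity matching is accepted practice, and nothing in the protocol is false or contradictory on this point. Checking standardised differences needs no outcome data, so a reader who infers outcome-driven adjustment goes beyond the text. A numerical threshold may sit in an analysis plan that is not shown, and its absence is not counted here. All of this stands.

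The bias also depends on chosen conditions. It needs several imbalances in one direction; with mixed directions it nearly vanishes. The 12 000 is a count of patients, while matching draws on records, and some patients supply more than one; a larger effective pool shrinks the bias. The authors may also change the matching method or ratio. This stands, and it limits the claim to what could happen.

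A reader might infer that objective 1 has no adjusted analysis. It has one, in the cohort with both groups matched to TORCH. That is a different cohort, though, and the validation section does not say which analysis decides. The statement about further adjusting for healthcare utilisation sits in the propensity score paragraph and most naturally means inclusion in the score.

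A reader might also infer that lost precision endangers objective 1. It does not: "The estimated sample size is ~12 000, which will provide ample power for the main outcomes of interest", and step 7 agrees. Nor can the simulated sizes be carried to objectives 2 and 3, where the TORCH-matching step is dropped and the group ratio will differ.

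**Conclusion.** The point holds as a cheap improvement in robustness. In the propensity-matched analyses, adjustment is contingent and discretionary, and measured imbalance below the trigger remains in the rate ratio that is judged against TORCH.

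Under same-direction imbalance on five covariates (largest residual difference about 0.05 to 0.08), a true 0.75 is estimated as about 0.77 to 0.78 with coverage of about 55 to 87%. Under mixed directions or closer matching the effect is small. The covariate effects, their directions, the dispersion and the imbalance before matching are all assumptions.

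The stronger reading, that the validation of a TORCH-sized effect is in danger, is not supported: 0.75 passes in every simulated setting. The decision is exposed if the true effect is about 0.85 to 0.9, which the protocol's own expectation of a weaker effect in routine care makes plausible, or in the narrow SAL band, whose limits lie only about 0.08 from 0.88 on the log scale.

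**What to change.** In Methods of analysis, replace the conditional sentence with a default. Outcome models in every propensity-matched cohort are adjusted, whatever the standardised differences, for a covariate list fixed before any outcome is analysed. The list should hold the TORCH matching variables, including exacerbation history, and the propensity score covariates. Using that whole list, without selecting by association with the outcome, leaves no choice to be made later.

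In Validation of results against TORCH, name the adjusted estimate from the propensity-matched cohort as the one held to the criteria. Report the unadjusted matched estimate beside it, and state the supporting role of the analysis with both groups matched to TORCH.

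The cost is a few sentences and little analysis work, since the covariates are already to be taken from CPRD. The log-link rate ratio should keep essentially the same meaning. Cox hazard ratios become conditional on the covariates, which should be stated. Adjustment does nothing about unmeasured confounding.

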#### Validation of results against TORCH

We will validate our findings against TORCH as part of objective 1 by determining whether results of the CPRD FP/SAL versus no FP/SAL treatment analysis are compatible with the TORCH exacerbations rate ratio for FP/SAL versus placebo (0.75; 95% CI 0.69 to 0.81). This outcome has been selected as it is an outcome of key significance for people with COPD^4^ and the result in TORCH shows a clear benefit with 95% confidence limits below 1. We have set two criteria that must be met for us to conclude results are consistent. First, the effect size must be clinically comparable with TORCH findings; the rate ratio for exacerbations in CPRD must be between 0.65 and 0.9. This range is deliberately not symmetrical around the TORCH estimate of 0.75 as we would anticipate the treatment effect in routine clinical care may be weaker than that seen in the optimised setting of a randomised trial. We recognise this rule could be met with a poorly powered, inconclusive result, so a second criterion is that the 95% CI for the rate ratio must exclude 1. If we go on to compare FP/SAL with SAL alone (see the ’Exposures, outcomes and covariates' section, ’Exposures' subheading), the 95% CI would also need to exclude 1, and the rate ratio would need to be between 0.81 and 0.95 (compared with the TORCH FP/SAL vs SAL result of 0.88, 95% CI 0.81 to 0.95).

#### Handling measurement of adherence to medication

Adherence to issued prescribing in general practice is likely to vary according to the treatment issued, for example, short course antibiotic treatment is notoriously not well adhered to, whereas long-term life-saving treatment such as antiretroviral medication is more likely to be taken as prescribed. While we do not have figures for adherence for COPD medication in UK general practice, we are able to estimate the proportion of time covered by prescribing as a proxy for adherence and will account for this in our analyses. Moreover, our intention is to estimate the effect of prescribing at the population level, and to some extent, the clinical effects we will measure are in part due to pharmacological effects, and in part the way the treatment is taken which includes adherence. Also of note, prescribing for COPD in the UK is predominantly through GPs and so we will not be missing prescribing information from other potential sources of treatment.

The data analysis for adherence will necessarily be a significant element of the work to be done for this study. However, we have reviewed the records for a random sample of 30 people with COPD starting treatment with FP/SAL to look at adherence patterns over the course of a year. Of the 30 patients, 20 (67%) were still receiving Seretide (FP/SAL) 1 year after starting treatment. Of the 20 who received Seretide for a full year, 15 (75%) received sufficient prescriptions to suggest at least 50% adherence over the year and 8 (40%) had sufficient prescriptions to suggest 80% adherence or higher. As expected, this suggests two things: first, adherence is likely to be poorer in routine clinical care than in the trial population; in TORCH 80% of participants were estimated to have adherence at 80% or higher. Second, there is a wide range of adherence in routine care. This will allow us to estimate both the population-level effects of treatment as actually used in routine care and to estimate the treatment effect in patients with more similar levels of adherence to TORCH participants. While we acknowledge that prescribing can only be a proxy for used medication, we believe it is not an unreasonable assumption that the amount of medication prescribed is correlated with the amount consumed. We plan to assess adherence for the cohort that we select for objective 1 beyond 1 year and report the findings. In the event that objective 1 detects a null or poorer treatment effect than anticipated (rate ratio >0.9), we will conduct a sensitivity analysis restricted to people estimated to be covered by FP/SAL treatment for 80% of their follow-up.

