### Exposures, outcomes and covariates

#### Exposures

For all objectives, exposures will be determined using CPRD prescribing records and code lists for COPD treatments (codelists provided in online supplementary material).

For objective 1, use of FP/SAL (trade name Seretide) is the primary exposure of interest and will be compared with no treatment with FP/SAL. We will limit included patients to those receiving Seretide 500/50, the dose used in TORCH. This information is recorded for all prescriptions of Seretide and this dose is the only currently approved dose for COPD in the UK (although we recognise some prescribing may not follow the licensed indication). If the results for our FP/SAL versus no treatment comparison are not consistent with the TORCH FP/SAL versus placebo results (see the ’Statistical analysis' and ’Validation of results against TORCH' sections for a definition of consistent), we will perform additional analyses where instead of using a no-treatment comparator group, our objective 1 comparator group will be people exposed to SAL, one of the other comparator groups from the TORCH trial.

As a secondary analysis in objective 1, other treatments for COPD will also be compared with no treatment. Selection of unexposed and exposed people for each of these drugs will follow steps 1–6 detailed above in the ’Selection of participants—objective 1' section, although step 3 will be omitted (as these cohorts will not need to be matched to TORCH). The other treatments we plan to include are as follows:LABALAMALABA+LAMA LABA+ICS other than FP/SALLABA+LAMA+ICS.

For objectives 2 and 3, we will again use recorded prescribing information to determine the dose received. We will be reliant mostly on the strength of each individual drug, which is recorded automatically against each product and does not require general practitioners (GPs) to enter these data, ensuring completeness. We will then be able to stratify analyses based on the dose prescribed. Specific exposures for objectives 2 and 3 are as follows (all vs no treatment):FP/SALLABALAMALABA+LAMA LABA+ICS LABA+LAMA+ICS.

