#### Misclassification of drug exposure periods and outcome status

It is possible that an individual may still be exposed to FP/SAL for some time after a prescription has finished, for example, if they have medication at home that they have not used from a previous prescription. This would mean that people may become eligible for inclusion in the unexposed group while they are actually still exposed. If our result differs from the TORCH results (eg, a rate ratio <0.65 or >0.9), we will conduct a sensitivity analysis in which we include an additional (grace) exposed period equivalent to the length of a single prescription at the end of each actual exposed period, and only classify individuals as eligible for inclusion as unexposed at the end of this additional period.

Our results could also be impacted by misclassification of outcome, given the routine nature of the data. Our initial approach for detection of COPD exacerbations is to use a validated case definition from previous work that maximises positive predictive value while maintaining a relatively high sensitivity.^12^ If our result differs from the TORCH results, we will consider performing a sensitivity analysis in which we assess the impact of applying alternative case definitions for COPD exacerbations (see online supplementary material for an overview of articles relating to the case definitions we plan to use, including any validity measurements provided).

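### The adherence analysis runs only if objective 1 gives a rate ratio above 0.9, and it selects treated patients on FP/SAL coverage during follow-up, so its result can be biased in either direction and may seem to agree with TORCH when there is no effect

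*Protocol article*

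**What the plan says.** The validation rule (Validation of results against TORCH) has two parts: "the rate ratio for exacerbations in CPRD must be between 0.65 and 0.9", and "a second criterion is that the 95% CI for the rate ratio must exclude 1".

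The adherence section sets the trigger: "In the event that objective 1 detects a null or poorer treatment effect than anticipated (rate ratio >0.9), we will conduct a sensitivity analysis". That analysis is "restricted to people estimated to be covered by FP/SAL treatment for 80% of their follow-up". The same section says that the spread of adherence will let the authors estimate the effect at adherence closer to that of TORCH participants.

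Methods of analysis applies an intention-to-treat principle to all analyses: "they will remain assigned to that exposure category for the entire duration of their follow-up".

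Other objective 1 analyses also depend on disagreement with TORCH:
- Grace period (Misclassification of drug exposure periods and outcome status): "If our result differs from the TORCH results (eg, a rate ratio <0.65 or >0.9), we will conduct a sensitivity analysis".
- Alternative exacerbation definitions (same section): these will only be considered.
- SAL comparator (Exposures): "we will perform additional analyses where instead of using a no-treatment comparator group, our objective 1 comparator group will be people exposed to SAL". It has its own acceptance window of 0.81 to 0.95.

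Three objective 1 analyses do not depend on the result: the 1-year asthma exclusion (Step 1), the approach that matches both groups to TORCH (Step 6), and the complete-record and multiple-imputation analyses (Missing data).

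**The concern.** Two features of the adherence analysis combine badly.

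First, the trigger is one-sided. It fires above 0.9 and not below 0.65, whereas the grace-period trigger covers both directions. The analysis is therefore seen only when the primary result is weaker than hoped.

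Second, the restriction uses a variable that is complete only at the end of follow-up. Patients who stay on treatment may differ in prognosis from those who stop, and exacerbations may themselves change prescribing. Follow-up also ends at death, transfer out or last collection, so a short record reaches 80% coverage more easily. An untreated patient cannot meet an FP/SAL coverage condition, so nothing parallel happens in the comparator. The propensity score balances the groups at the index date, not a subset of one group chosen later.

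The restricted rate ratio thus mixes the effect of better adherence with the prognosis of people who adhere. What is at stake is the validation claim: the caption to Figure 1 carries the validated techniques into objectives 2 and 3, whose populations TORCH excluded or under-represented.

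**Working it through.** **Pilot figures.** The adherence section reports 20 of 30 starters still treated at one year (67%). Of those 20, "8 (40%) had sufficient prescriptions to suggest 80% adherence or higher": 8/20 = 40%, as stated. Among all starters the share is 8/30 = 26.7% (exact 95% CI 12% to 46%), if none of the ten who stopped reached 80%. Applied to about 6000 treated patients, 6000 × 8/30 = 1600 remain. In TORCH, 80% of participants were at that level.

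**Inputs from the protocol.** About 6000 per group (Step 6), 0.5 exacerbations per patient-year (Sample size), 3 years (Methods of analysis), so 1.5 expected events per patient.

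**Assumptions, not in the protocol.** No drug effect. Underlying rates are lognormal with frailty variance k = 0.5, 1 or 2, so the SD of the log rate is s = √ln(1+k) = 0.637, 0.833 or 1.048. Coverage has correlation ρ with a lower log rate. The top p = 8/30 on coverage are kept and compared with all untreated patients.

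**Formula.** With c = 0.623 the normal cut-off for the top 8/30, restricted RR = Φ(−c − ρs)/p. Example, k = 1, ρ = 0.10: Φ(−0.623 − 0.083) = Φ(−0.706) = 0.240, and 0.240/0.2667 = 0.90.

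| ρ | k = 0.5 | k = 1 | k = 2 |
|---|---|---|---|
| 0 | 1.00 | 1.00 | 1.00 |
| 0.10 | 0.92 | 0.90 | 0.88 |
| 0.15 | 0.89 | 0.85 | 0.82 |
| 0.20 | 0.85 | 0.81 | 0.76 |
| −0.10 (high coverage marks sicker patients) | 1.08 | 1.11 | 1.13 |

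The correlation that gives exactly 0.9 is 0.13, 0.10 and 0.08 for k = 0.5, 1 and 2. Put another way, retained patients need only a 10% lower underlying rate than all treated patients.

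**Interval criterion.** For 1600 against 6000 patients and RR 0.90, SE(log RR) = √[1/(1600·1.5·0.9) + k/1600 + 1/(6000·1.5) + k/6000]. For k = 1 this is 0.037, and the 95% CI is 0.84 to 0.97. For k = 0.5 it is 0.85 to 0.96, and for k = 2 it is 0.82 to 0.99. At this sample size, excluding 1 gives little protection.

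**Simulation.** 1000 data sets per setting, no drug effect. The as-assigned analysis gave RR 1.00, exceeded 0.9 in at least 99.9% of runs and met both criteria in at most 0.1%. The restricted analysis met both criteria as follows.

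| ρ | k = 0.5 | k = 1 | k = 2 |
|---|---|---|---|
| 0 | 0.1% | 0.2% | 1% |
| 0.10 | 21% | 51% | 71% |
| 0.15 | 71% | 93% | 99% |
| 0.20 | 96% | >99% | >99% |

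**Retained share.** With the pilot limits in the same formula, ρ = 0.10 gives RR 0.90 to 0.84 if 12% are kept and 0.95 to 0.91 if 46% are kept. At ρ = 0.20 the ranges are 0.81 to 0.69 and 0.89 to 0.82. The size depends on the share retained, but the mechanism does not.

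**The case against.** The strongest reply is that the protocol calls this a sensitivity analysis, states its purpose openly, and ties the verdict to the FP/SAL versus no-treatment comparison. Only the SAL comparison receives a second acceptance window. A reader might infer that a restricted result inside 0.65 to 0.9 would overturn a failed validation. The text does not say so. What stands is that nothing excludes it, in a study whose main product is that verdict.

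A reader might also infer that every extra analysis follows failure, so that none could contradict a success. That is wrong: the asthma-window, double-TORCH-matched and missing-data analyses run regardless. None, however, is given a stated role in the verdict.

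The direction of bias is not known. The protocol gives no relation between adherence and prognosis, and heavier prescribing may mark sicker patients. A claim that the restriction favours benefit is not supported; it can distort either way.

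A condensed article may leave re-matching or covariate adjustment to a fuller plan. The protocol does say that adherence will be accounted for and that models may be further adjusted. So the absence of that detail is not the complaint. The complaint is with what the article does fix: the one-sided trigger, and selection on coverage over the patient's own follow-up.

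Finally, the 27% is a one-year figure from 30 records applied to three years.

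**Conclusion.** The point holds as a design weakness in a conditional analysis, not as proof that the validation will be wrong. The protocol fixes a one-sided trigger at the upper failure limit, and a restriction on a post-index variable that only treated patients can meet. With no drug effect, an assumed correlation of 0.10 to 0.20 between coverage and better prognosis gives a restricted rate ratio of about 0.92 to 0.76, often meeting both validation criteria. The opposite sign at 0.10 gives 1.08 to 1.13. These figures rest on an assumed frailty variance of 0.5 to 2, an assumed correlation, and 27% retained. With zero correlation this mechanism gives no bias. The protocol leaves open, rather than states, whether agreement found this way may count towards consistency.

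**What to change.** 1. Run the adherence analysis whatever the primary rate ratio.
2. Replace the restriction with a per-protocol analysis that censors at deviation from assigned exposure in both groups, with inverse-probability weights for baseline and time-varying predictors of adherence. A landmark version (coverage measured in an initial window, events counted afterwards) deals with reverse causation and short follow-up. It does not remove a stable link between adherence and prognosis: the formula above contains no time term, so the bias is the same after the landmark. It is acceptable only with re-matching or adjustment for those predictors.
3. State in the validation section that the primary FP/SAL versus no-treatment analysis alone decides consistency. Report any later agreement, including the SAL comparison, separately as evidence obtained after the primary result failed.

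The cost is wording and a few extra runs on data already held. Weighting will widen the intervals.
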